## Abstract

**Background:**

In certain clinical situations, root canal treatment in teeth with apical periodontitis is performed in multiple visits, with the use of intracanal dressing between visits, aiming to reduce microorganisms and their by-products of the root canal system prior to filling. However, in recent years, discussions have been growing about the real need for the use of intracanal dressing in these cases. The use of ultrasonic activation of the auxiliary chemical substance has increased the potential for decontamination promoted during the chemomechanical preparation of the root canal. Thus, this study is designed to explore whether the use of intracanal dressing between visits during endodontic treatment favors periradicular repair in teeth with apical periodontitis.

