### Trial design {8}

This is a randomized, double-blinded, paralell group, non-inferiority controlled trial.

The trial protocol conforms with the Consolidated Standards of Reporting Trials (CONSORT) Statement. The trial design and protocol adhere to the Standard Protocol Items of the Recommendations for Interventional Trials (SPIRIT) criteria.

The study aims to compare the efficacy of endodontic treatments conducted in a single visit using ultrasonic irrigant activation and in two visits also using ultrasonic irrigant activation, with and without the use of calcium hydroxide dressing, in lower molar teeth with asymptomatic apical periodontitis (Fig. 1, “Study flowchart”).

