## Sample size and statistical methods

### Sample size details

The required sample size was calculated based on the preliminary outcome parameter of success, in a sequential approach, with each clinical case (tooth) serving as the statistical unit. Clinical studies that allow us to estimate, by means of CBCT, the repair index (complete absence of periapical radiolucency), therefore the success, after endodontic treatment of teeth with apical periodontitis and periradicular lesion, state that it is necessary to have a follow-up of at least 2 years to determine the success or failure of the treatment [22, 23]. After the first year of follow-up, post-endodontic treatment, it is still possible to observe the presence of periapical radiolucency in 52 to 84% of cases [1, 24, 25]. The sample will consist of 210 mandibular molars (first or second molars), based on statistical sample calculation, considering a power of 80%, an alpha value of 0.05, and an effect size of 20%. All patient characteristics at the beginning of treatment, such as age, gender, lesion size, among others, will be considered in the statistical analysis, in order to confirm the randomization of groups and the possible confounding effect of these characteristics.

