#### Main outcome analysis

The inter-group comparison of success rates will be analyzed using the Kruskal-Wallis test at 5% of the level of significance. For the missing data, the last observation carried forward (LOCF) method will be adopted to fill the validity analysis.

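### The trial is labelled non-inferiority, but its only primary test is a three-group test of equality with no margin, so no result of that test can support a non-inferiority conclusion

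*Protocol article*

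**What the plan says.** Trial design {8}: "This is a randomized, double-blinded, paralell group, non-inferiority controlled trial".

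Main outcome analysis, under {20a}: "The inter-group comparison of success rates will be analyzed using the Kruskal-Wallis test at 5% of the level of significance". No other comparison of the primary outcome is described. Section {20b} plans no additional analyses, and {20c} adds only sensitivity analyses for missing data.

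Sample size details: "The sample will consist of 210 mandibular molars (first or second molars), based on statistical sample calculation", and then "considering a power of 80%, an alpha value of 0.05, and an effect size of 20" per cent. The text does not call the 20% a margin. It gives no pair of arms, scale or direction for it, no expected 24-month success rate and no sidedness for alpha. The only rate nearby concerns the first year, when "it is still possible to observe the presence of periapical radiolucency in 52 to 84% of cases".

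Sequence generation {16a} sets three equal groups of 50 participants (70 teeth). The objectives in {7} and {8} speak only of evaluating or comparing the three approaches. Section {6b} describes multi-visit treatment with dressing as the traditional approach and the single session as the comparison group, but neither is named as a non-inferiority reference.

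**The concern.** A non-inferiority trial asks whether a new approach is worse than a reference by less than a margin fixed in advance. It needs a reference arm, a margin, a direction and a rule that sets an interval or one-sided test against the margin. The planned Kruskal-Wallis test has none of these. It asks whether the three arms differ in any way.

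The label and the analysis therefore point to different hypotheses. A significant result says that some arm differs. A non-significant result says only that a difference was not detected, and that becomes more likely as the trial gets smaller or noisier. The choice at stake is whether a visit or a dressing can be omitted, so a real deficit in healing could go undetected while the trial still carries the non-inferiority label.

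**Working it through.** **1. The plan's own sample size.** Inputs stated: 210 teeth, 70 per arm, 80% power, alpha 0.05, effect size 20%. The figure cannot be reproduced uniquely, because the base rate, the sidedness and the meaning of 20% are missing.

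- Read as a 20-point difference between two proportions (two-sided, no continuity correction), the need is 49 to 97 per arm over the base rates tried.
- Read as a standardised effect, f = 0.2 for three groups needs 244 in total; w = 0.2 needs 241 (2 df) or 196 (1 df).
- Read as a 20-point margin (one-sided 0.025), 70 per arm falls between an assumed success of 75% (74 per arm) and 80% (63 per arm). Neither rate is in the protocol.

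So the sample-size text does not show that the trial was sized for non-inferiority.

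**2. What the planned test can show.** For success or failure data the Kruskal-Wallis statistic is

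H = ((N − 1)/N) × Σ (xᵢ − n p̄)² / (n p̄(1 − p̄)),

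referred to chi-square with 2 df (critical value 5.99). No margin enters it.

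Hypothetical example: 56/70, 56/70 and 46/70 successes.

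- p̄ = 158/210 = 0.752 and n p̄ = 52.67.
- Squared deviations sum to 11.11 + 11.11 + 44.44 = 66.67.
- H = (209/210) × 66.67/13.04 = 5.09, p = 0.079: not significant.
- Pairwise difference: 46/70 − 56/70 = −14.3 points; standard error √(0.8 × 0.2/70 + 0.657 × 0.343/70) = 0.0742.
- 95% CI: −14.3 ± 1.96 × 7.42 = −28.8 to +0.3 points.

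The test does not reject, yet the data do not exclude a deficit of more than 20 points.

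**3. How often a real deficit goes undetected.** H was simulated with 70 independent teeth per arm and one arm truly worse. All success rates are assumptions.

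| Success in the other two arms | 10 points worse | 15 points worse | 20 points worse |
|---|---|---|---|
| 90% | 60% | 29% | 10% |
| 80% | 72% | 46% | 22% |
| 70% | 77% | 53% | 29% |
| 60% | 79% | 57% | 31% |
| 50% | 79% | 57% | 30% |

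Entries are the percentage of trials with a non-significant test.

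**4. With loss to follow-up.** Section {20c} counts missing as failure, which keeps 70 teeth per arm. With 20% loss in every arm and 80% success otherwise, the observed rate is 0.8 × 80% = 64%. In an arm 15 points worse it is 0.8 × 65% = 52%, so the deficit shrinks to 12 points. The test is then non-significant in about 70% of trials (about 85% for a true 10-point deficit and 51% for 20).

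**5. What 70 per arm can deliver for non-inferiority.** For one contrast with equal true success p, one-sided 0.025 and 80% power:

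smallest margin = (1.960 + 0.842) × √(2p(1 − p)/70).

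| Assumed success | Smallest margin |
|---|---|
| 90% | 14.2 points |
| 80% | 18.9 points |
| 70% | 21.7 points |
| 50% | 23.7 points |

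At 80% success, power is 32%, 60% and 84% for margins of 10, 15 and 20 points. These figures ignore clustering of 210 teeth within 150 patients.

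**The case against.** The strongest reply is that non-inferiority appears once, as a label. The abstract, objectives and discussion say evaluate, compare or explore, and the plan could be read as a three-arm test of difference with one stray word. That is possible. If so, the word should go, because it states a design that the analysis does not carry out.

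A second reply is that an article condenses a fuller protocol, and that a margin, an interval rule or a per-protocol set may stand in a document not shown. This has force for details that are merely absent, and a missing per-protocol set is not held against the plan here. It does not remove the conflict. The article itself states both the design and the primary test, and a later document with a margin rule would have to replace that test.

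Three stronger readings are tempting and not supported:

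- A reader might infer that the protocol intends to treat p > 0.05 as proof of no worse. No such rule is written; it would be a guess about later reporting.
- A reader might take the 20% as the margin, so that single-visit treatment could be 20 points worse and pass. The text calls it an effect size and ties it to no contrast. Even as a margin, it would not be used by the Kruskal-Wallis test.
- A reader might take the abstract's aim, to explore "whether the use of intracanal dressing between visits during endodontic treatment favors periradicular repair", as a formal superiority hypothesis. It is background wording and adds little.

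**Conclusion.** The contradiction holds. The design statement says non-inferiority; the stated primary test examines equality; the sample-size basis is not defined as a margin. As written, no result of the primary test supports a non-inferiority conclusion, and a non-significant p-value is not evidence for one.

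The logical conflict needs no assumption. Its practical size does: with 70 independent teeth per arm, a true 15-point deficit in one arm is missed in about 30% to 57% of trials for success of 90% down to 50% elsewhere. The protocol gives no 24-month success rate, so the range matters more than any single value. It also gives no allowance for dropout, so the 20% loss in the worked scenario is an illustration.

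**What to change.** Choose one of two routes.

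**(a) Keep non-inferiority.** Name two visits with dressing as the reference arm. State which contrast or contrasts decide (single visit against reference, no dressing against reference) and how multiplicity is handled. State a clinically justified margin on the absolute difference in 24-month success. Claim non-inferiority only if the lower limit of the two-sided 95% confidence interval lies above minus that margin. In the sample-size section, restate the power of 70 teeth per arm for that margin, with the assumed success rate and the allowance for clustering.

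**(b) Drop it.** If no defensible margin is attainable at this size, delete non-inferiority from {8}, report pairwise risk differences with 95% confidence intervals, and state that a non-significant test does not show the arms to be equivalent or non-inferior.

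**Cost.** Either route is a change of wording with no new procedures. Under (a) the stated power becomes less favourable for smaller margins: a 10-point margin at 80% success would need about 252 teeth per arm, against 70 planned. Section {25} requires a favourable ethics opinion before an important amendment is implemented. Recruitment began in August 2021, so the amendment should be dated and made before unblinding, with the margin justified without reference to trial outcome data.

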**Fig. 1 Fig1:**
[figure not shown]
Study flowchart. The trial will evaluate the effectiveness of endodontic treatments conducted in a single visit with the use of ultrasonic irrigant activation and in two visits with the use of ultrasonic irrigant activation and with and without the use of Ca(OH)2 dressing, in mandibular molars with asymptomatic apical periodontitis regarding periradicular repair during a period of 2 years of clinical, radiographic, and tomographic follow-up, based on the periapical index (PAI)

After obtaining informed consent, all eligible patients (*n* = 150) will be randomly divided into three groups, according to the clinical approach used during endodontic therapy: in group 1—root canal treatment in a single visit (RCT-SV): endodontic treatment in a single visit using chemomechanical preparation (rotary NiTi instruments, 5.25% NaOCl, 17% ethylene diamine tetraacetic acid (EDTA)) and passive ultrasonic irrigation (PUI), followed by obturation (gutta-percha and epoxy resin-based sealer) and final restoration (composite resin); group 2—root canal treatment in two visits with intracanal dressing (RCT-TVWD): endodontic treatment in two visits using chemomechanical preparation (rotary NiTi instruments, 5.25% NaOCl, 17% EDTA) and PUI, followed by intracanal dressing [Ca(OH)2 powder paste mixed with camphorated paramonochlorophenol (CPMC) and glycerin in 3:1:1 proportion] and temporary restoration (glass ionomer cement (GIC)) for 7 days. After 7 days, an identical chemomechanical preparation on visit 2 was performed, followed by obturation (gutta-percha and epoxy resin-based sealer) and final restoration (composite resin); and group 3—root canal treatment in two visits without intracanal dressing (RCT-TVWOD): endodontic treatment in two visits using chemomechanical preparation (rotary NiTi instruments, 5.25% NaOCl, 17% EDTA) and PUI, followed by temporary restoration with composite resin (in order to avoid contamination of the root canal system) for 7 days, without intracanal dressing. After 7 days, an identical chemomechanical preparation on visit 2 was performed, followed by obturation (gutta-percha and epoxy resin-based sealer) and final restoration (composite resin). The follow-up period will be 24 months, with clinical data collected soon after endodontic therapy. Patients’ preference in choosing the number of clinical visits and the satisfaction rate after completion of treatment will be noted. Patients’ postoperative pain levels will also be recorded in periods of 24, 48, and 72 h and 7 days. Subsequently, clinical findings and long-term follow-up evaluations, with periradicular repair, will be performed by IOPAR at 6 and 12 months and CBCT at 24 months of follow-up.

The primary objective of this study is to evaluate the efficacy of endodontic treatments carried out in a single visit with the use of ultrasonic irrigant activation and in two visits also with the use of ultrasonic irrigant activation and with and without the use of Ca(OH)2 dressing, in lower molar teeth with asymptomatic apical periodontitis. The secondary objective is to carefully investigate the factors influencing the clinical outcomes of a single-visit endodontic treatment of teeth with asymptomatic apical periodontitis and, at the same time, explore the clinical conduct in two visits also with the use of ultrasonic irrigant activation and with the use of intracanal dressing during endodontic therapy of teeth with asymptomatic apical periodontitis.

## Methods: participants, interventions, and outcomes

### Study setting {9}

The study will be conducted in the private offices of two of the co-investigators involved in the study ([name] and [name]), located in the cities of Itabuna (Bahia) and Goiânia (Goiás), Brazil, respectively. All investigators and examiners are specialists in Endodontics with more than 10 years of clinical experience. They will participate in this randomized clinical trial after receiving adequate training to obtain a comprehensive view of the principles and strategy of the 3 clinical approaches that will be used. A total of 150 adult patients, aged between 18 and 60 years old, who voluntarily seek endodontic treatment in the Brazilian Unified Health System in the cities of Itabuna, in the State of Bahia, and in Goiânia, in the State of Goiás, Brazil. After an assessment of eligibility and informed consent, patients will be randomly assigned to one of 3 clinical study groups. Patients who agree to participate in this study will sign an informed consent form.

### Eligibility criteria {10}

#### Inclusion criteria

To enroll in the study, subjects must (1) be diagnosed with apical periodontitis in lower molar teeth (first or second molars), the periradicular lesion with a diameter between 1 and 5mm analyzed through the real tomographic scale of 1:1; (2) be asymptomatic; (3) spontaneously agree and sign the informed consent form; (4) have an absence of any chronic systemic disease; and (5) be not taking antibiotics and anti-inflammatory drugs.

#### Exclusion criteria

Patients may not participate in the study if they are as follows: (1) teeth with extensive coronary destruction that makes direct restoration with composite resin unfeasible, (2) calcified teeth, (3) teeth with incomplete root formation, (4) teeth with persistent exudation, (5) teeth with anatomical complexities that prevent endodontic treatment in a single visit, (6) teeth recommended for endodontic retreatment, (7) teeth with advanced periodontal pocket, and (8) teeth in which foraminal patency is not obtained.

Patients who present a profile that fits to that described in the inclusion and exclusion criteria will then be referred for evaluation by other examiners ([name], [name], and [name], experts in Endodontics for more than 15 years), for confirmation of diagnosis and treatment planning, if necessary. Patients who do not fit the required profile will be forwarded to the health unit of origin. All the steps of interviews and clinical examination necessary to complete the diagnosis will be carried out by the examiners who will perform the treatment.

Patients with systemic diseases (diabetes, transplants, heart disease, liver failure, and kidney failure) and immunodepressed patients are prohibited during the trial as these conditions can affect the oral functions.

### Who will take informed consent? {26a}

All participants will be given an information sheet including the names and affiliations of the investigators, a description of the study, and its duration. They will have the right to withdraw at any time without giving reasons, ethics committee approvals, and the personal data privacy guarantee. Patients will have unlimited time to read the consent and ask questions. After the period of reflection, during the enrolment visit, the written informed consent will be signed.

### Additional consent provisions for collection and use of participant data and biological specimens {26b}

Not applicable (N/A). There was neither collection nor use of participant data and biological specimens.

## Interventions

### Explanation for the choice of comparators {6b}

Traditionally, root canal treatment in teeth with apical periodontitis is performed in multiple visits, with the use of intracanal dressing between visits, aiming to reduce microorganisms and their by-products from the root canal system prior to filling. However, this type of conventional endodontic treatment has as a disadvantage the inconvenience of requiring patient return (in multiple sessions) for medication changes, until the root canal filling is possible. In the comparison group, the root canal treatment will be performed in a single session, which represents a more objective form of treatment, with the convenience of only one appointment for the patient and a lower operating cost for the professional.

### Intervention description {11a}

In order to treat apical periodontitis, in the first visit, the same endodontic instrumentation protocol will be performed for all teeth randomly divided into the 3 study groups. What will vary will be complementary and additional maneuvers such as the use of ultrasonic activation and intracanal dressing between visits of endodontic instrumentation. All endodontic therapy procedures will be performed under a dental microscope, except for anesthesia and rubber dam placement steps.

#### First clinical appointment

The first visit will include the following clinical protocol depending on the study group: for the 3 groups (G1, G2, and G3): (1) Anesthesia and caries removal. After local anesthesia with articaine hydrochloride and epinephrine tartrate injection (with 1:200,000 adrenaline [Produits Dentaires Pierre Rolland, Merignac, France]), all decayed tissue from the tooth is removed. (2) Isolation and access preparation. The tooth is isolated with a rubber dam and disinfected, and the pulp chamber will be completely unroofed. (3) Initial irrigation with 5 ml of 5.25% NaOCl. (4) Root canal preparation. The #10 C-Pilot file will be used to perform the glide path along the length of the tooth on the radiograph, irrigated with 2 ml of 5.25% NaOCl, followed by rotary instrumentation with #15/.03, #25/.04, and #30/.05 NiTi files, initially in the cervical and middle thirds, after which the working length with the foraminal locator will be performed. Finally, the instrumentation of the apical third will be performed with the same sequence of NiTi rotary files used previously. (5) The canal will be copiously irrigated in three stages using 10ml of 5.25% NaOCl for each of thirds: cervical, middle and apical, totaling 30ml, followed by a final rinse with 10ml of 5.25% NaOCl stirred with the ultrasonic inserts and 10 ml of 17% EDTA stirred also with ultrasonic inserts. The final rinse will be carried out, according to Haapasalo et al. [21], with 10ml of 70% isopropyl alcohol.

##### Group 1—root canal treatment in a single visit (RCT-SV)

(1) The root canals will be filled in the first visit. In this group, a #30/.05 gutta-percha cone and epoxy resin-based sealer with the continuous heat wave technique and a final restoration with Z250 composite resin (3M ESPE, St. Paul, USA) will be used.

##### Group 2—root canal treatment in two visits with intracanal dressing (RCT-TVWD)

(1) The root canals will receive intracanal dressing with Ca(OH)2 (supplied by Farmácia Fórmula & Ação, São Paulo, Brazil), CPMC (Supplied by Farmácia Fórmula & Ação, São Paulo, Brazil), and glycerin (Supplied by Farmácia Fórmula & Ação, São Paulo, Brazil) paste for a period of 7 days. To restrict bacterial regrowth and supply continued disinfection, the root canal will be filled homogeneously to the working length with Ca(OH)2/CPMC/glycerin paste. The tooth will be shielded with glass ionomer cement (GIC) (Vidrion R, SSWhite, Rio de Janeiro, Brazil) as a temporary restoration.

##### Group 3—root canal treatment in two visits without intracanal dressing (RCT-TVWOD)

(1) The root canals will be without intracanal dressing for a period of 7 days, taking into account that the tooth will be restored with composite resin as a temporary restoration (in order to avoid contamination of the root canal system).

#### Second clinical appointment

The second visit will include the following clinical protocol depending on the study group: for the 2 remaining groups (group 2 and group 3): (1) Anesthesia and restorative material removal. After local anesthesia with articaine hydrochloride and epinephrine tartrate injection (with 1:200,000 adrenaline [Produits Dentaires Pierre Rolland, Merignac, France]), all temporary restorative material from the tooth is removed. (2) Isolation and access. The tooth is isolated with a rubber dam and the root canal will be accessed one more time.

##### Group 2

(1) After 7 days, the intracanal dressing will be removed and the root canal will receive a new chemomechanical preparation, identical to the one performed in the first visit, and then it will be filled and permanently restored similarly to group 1.

##### Group 3

(1) After 7 days, the root canal will receive a new chemomechanical preparation, identical to the one performed in the first visit, and then it will be filled and permanently restored similarly to group 1.

